## Abstract

Background: Lafora disease (LD) is an ultra-rare and fatal neurodegenerative disorder with limited therapeutic options. Current treatments primarily address symptoms, with modest efficacy in halting disease progression, thus highlighting the urgent need for novel therapeutic approaches. Gene therapy, antisense oligonucleotides, and recombinant enzymes have recently been, and still are, under investigation. Drug repurposing may offer a promising approach to identify new, possibly effective, therapies. Methods: This study aims to investigate the conditions for repurposing empagliflozin, an SGLT2 (sodium/glucose cotransporter-2) inhibitor, as a potential treatment for LD and to establish a clinical protocol. Clinical phase: This 12-month prospective observational study will assess the safety and clinical efficacy of empagliflozin in two patients with early to intermediate LD stage. The primary endpoints will include changes in the severity of epilepsy and cognitive function, while the secondary endpoints will assess motor function, global function, and autonomy. Multiple clinical and instrumental evaluations (including MRI and PET with ^18^F-fluorodeoxyglucose) will be performed before and during treatment. Safety monitoring will include regular clinical assessments and reports of adverse events. Preclinical phase: In silico studies (using both molecular docking calculations and reverse ligand-based screening) and in vitro cell-based assays will allow us to investigate the effects of empagliflozin (and other gliflozins) on some key targets likely implicated in LD pathogenesis, such as GLUT1, GLUT3, glycogen synthase (hGYS), and glycogen phosphorylase (GP), as suggested in the literature and digital platforms for in silico target fishing. Results: The expected outcome of this study is twofold, i.e., (i) assessing the safety and tolerability of empagliflozin in LD patients and (ii) gathering preliminary data on its potential efficacy in improving clinical and neurologic features. Additionally, the in silico and in vitro studies may provide new insights into the mechanisms through which empagliflozin may exert its therapeutic effects in LD. Conclusion: The findings of this study are expected to provide evidence in support of the repurposing of empagliflozin for the treatment of LD.

## 1. Introduction

Lafora disease (LD, OMIM 254780, ORPHA 501) is an ultra-rare, genetically inherited (autosomal recessive), and fatal form of progressive myoclonic epilepsy [1]. LD is characterized by rapid neurological deterioration linked to the progressive appearance of insoluble glycogen-like inclusions (polyglucosan), known as Lafora bodies (LBs), in the brain and peripheral tissues [2]. Mutations in two genes, *epm2A* and *epm2B/NHLRC1*, located on chromosome 6 and encoding laforin and malin, two proteins involved in glycogen metabolism, are responsible for the gradual accumulation of LBs and subsequent neurodegeneration [3].

The prevalence of LD is estimated at about 300 cases worldwide, but this number is likely underestimated due to diagnosis uncertainty. LD is relatively more frequent in Mediterranean countries, particularly in Italy. According to data from the Italian Lafora Association (AILA), there are currently 25–30 patients in Italy, with about one-third located in Apulia, a region in southeastern Italy [4]. Furthermore, there is a higher prevalence of mutations in the *epm2B* gene in Italian patients, suggesting a potential founder effect for certain pathogenic variants. In the Apulia region, specifically, at least two clusters of patients with the same type of mutation have been identified [4].

LD typically appears in individuals between the ages of ten and fifteen, who initially have a normal neurodevelopment, followed by generalized tonic–clonic seizures, visual focal seizures, and myoclonus. Diagnosis is often delayed, and distinguishing LD from juvenile myoclonic epilepsy can be difficult [4]. As the disease progresses, epilepsy becomes refractory and is associated with continuous myoclonus and progressive neurological deterioration with dementia, ataxia, and photosensitivity. Gradually, patients enter a vegetative state, with death occurring within eleven years of symptom onset [5] due to neurological problems such as refractory or super-refractory status epilepticus or medical complications like aspiration pneumonia [6].

The optimal therapy for LD should be based on early intervention to prevent rapid neurological decline and to inhibit the formation of LBs, which underlie neurodegeneration. Currently, the only available therapeutic approaches in LD are symptomatic and ineffective at halting disease progression, and they are usually performed at a late stage of the disease. These treatments mainly involve anti-seizure medications, with metformin and the ketogenic diet being additional options. The antidiabetic drug metformin received orphan drug designation for LD in 2016 by EMA (EU/3/16/1803) and in 2017 by FDA (12/14/2017), based on the efficacy found in animal models of LD, which have shown a mechanism of action partly dependent on the indirect activation of AMP-activated protein kinase (AMPK). However, the effectiveness of metformin in treating LD patients remains unclear, possibly due to its administration at a medium-advanced stage of the disease. Early treatment might likely provide better results in slowing disease progression [7,8,9]. The ketogenic diet, which promotes the production of neuroprotective ketone bodies and limits glucose intake, may reduce glycogen synthesis, potentially decreasing polyglucosan accumulation and slowing down the disease progression. Nevertheless, efficacy data obtained from mouse models have not been confirmed in humans, as the ketogenic diet has been tested in patients with advanced LD [10,11].

Innovative therapeutic approaches are currently being evaluated in animal models and human trials and are based on the reduction in brain glycogen synthesis (antisense oligonucleotides), replacement of the non-functional gene (gene therapy), improvements in proteostasis, and neuroinflammation [12,13,14,15]. Recombinant enzymes capable of degrading glycogen and promoting the degradation of LBs are also being investigated [16]. VAL-041 (Valerion Therapeutics) is an antibody–enzyme fusion protein that combines α-amylase (an enzyme involved in pancreatic polyglucan degradation) with an antibody fragment (Fab) to enhance penetration into brain cells. This fusion protein was tested successfully in the *epm2a*-/- mouse. Some Italian LD patients are being treated with the drug rhGAA (recombinant human α-glucosidase, Myozyme^®^), a drug approved by the FDA for Pompe disease, to help degrade lysosomal glycogen. A clinical trial is also underway in Italy with VAL-1221 (Valerion Therapeutics and Parasail), another antibody-enzyme fusion protein based on rhGAA and Fab (EudraCT number 2023-000185-34; Drug discovEry and repurposing to Find a trEAtmenT for Lafora Disease—DEFEAT-LD—PNRR-MR1-2022-12376430). Despite their potential, these innovative therapies face significant challenges in terms of costs and treatment timeline, which are especially critical for a rapidly progressing and fatal disease like LD.

Drug repurposing, a strategy aimed at identifying existing drugs approved for other indications and testing them for new therapeutic uses, may also offer a solution for rare diseases [17]. This approach is expected to reduce both the time and cost of drug development, as repurposed drugs are already approved for use and can be directly tested in preclinical and clinical studies for new pathological conditions, such as rapidly progressing diseases like LD.

The aim of this study is to investigate the effects of empagliflozin, a sodium-glucose cotransporter 2 (SGLT2) inhibitor belonging to the gliflozin class, for the treatment of LD. Figure 1 shows the binding mode of empagliflozin into the binding site of the SGLT2 protein (PDB_CODE: 7VSI [18]), as revealed by the crystallography of the ligand–protein complex. Three key hydrogen bonds between the HB-donors 2-OH, 3-OH, and 6-OH of the glucose moiety with the respective HB-acceptors in the side chains of E99, K321, and Q457, along with hydrophobic interactions, stabilize the ligand–receptor complex.

Gliflozins promote renal glucose excretion and exhibit pleiotropic effects. They are indeed approved for treating type 2 diabetes, heart failure, and chronic kidney disease. The potential use of gliflozins in LD is supported by the literature’s data [19]. Several studies have demonstrated the neuroprotective effects of gliflozins in animal models of Alzheimer’s disease and cerebral ischemia through various mechanisms [19,20]. Interestingly, a body of experimental evidence supports the repositioning of empagliflozin for the treatment of glycogen storage disorder (GSD). Empagliflozin has been successfully repurposed in both paediatric and adult patients with GSD type Ib to treat neutropenia and neutrophil dysfunction caused by the accumulation of 1,5-anhydroglucitol-6-phosphate. It has also shown positive effects in improving bowel inflammation in some patients, leading to the amelioration of the quality of life for both patients and caregivers, with good tolerability [21,22,23,24,25,26,27,28]. In addition, a clinical trial testing the effects of empagliflozin in epilepsy is ongoing (NCT05512130). Furthermore, a recent preclinical study using an animal model of LD demonstrated the translational potential of gliflozins in LD patients [29]. Specifically, gliflozins, including empagliflozin, have shown beneficial effects on neuronal hyperexcitability and impaired locomotor activities, key pathological features of LD.

Here, we present the study protocol for administering empagliflozin to LD patients, along with in silico and experimental in vitro approaches adopted to verify its potential in the treatment of LD. The results of this study may provide critical evidence in support of the repurposing of empagliflozin for the treatment of LD.

## 2. Experimental Design

### 2.1. Study Design and Setting

**Objective 1:** The first objective is to evaluate the safety and tolerability of empagliflozin in patients with genetically diagnosed LD in the early to intermediate stages over a 6-month treatment period. Efficacy will be assessed by monitoring changes in the frequency and intensity of epileptic seizures; variations in the background activity and frequency of epileptiform abnormalities on an electroencephalogram (EEG); stabilization of cognitive, behavioral, and motor outcomes, as well as neuro-radiological and metabolic biomarkers (including high-field brain MRI—3 Tesla, brain PET with ^18^F-fluorodeoxyglucose—FDG).

**Objective 2:** The second objective is to investigate the effect of empagliflozin (and SGLT2 inhibitors in general) on targets involved in glucose metabolism and the pathogenesis of LD, aiming to uncover new mechanisms of action and to further support the repurposing of gliflozins in the treatment of LD. Specifically, considering the dysfunctional cellular pathways related to the formation of LBs, two brain glucose transporters (GLUT1 and GLUT3) and glycogen synthase (hGYS) will be explored [30,31]. The interaction with these targets will be evaluated through molecular docking studies, while the ability of gliflozins to reduce intracellular concentrations of glucose and glycogen will be evaluated through in vitro studies using various cell lines.

### 2.2. Eligibility Criteria

A single-center, observational, controlled pilot study will be conducted at the Neurology Unit of IRCCS Casa Sollievo della Sofferenza Hospital in San Giovanni Rotondo (Foggia, Italy). The stage of disease progression will be assessed using a disability scale that considers cognitive and motor functions, activities of daily living, and social interaction [32,33]. The stages are defined as follows: 1—mild cognitive and motor deterioration: preserved activities of daily living and social interaction; 2—moderate cognitive deterioration: limitations in motor activities and social interactions; 3—severe cognitive and motor deterioration: need for assistance with walking and activities of daily living and poor social interaction; 4—wheelchair-bound or bedridden patients: no significant activities of daily living and social interaction. Patients will be enrolled based on the following criteria:

Inclusion Criteria:
Documented genetic diagnosis of LD (pathogenic mutations in the EPM2A or EPM2B genes);Age: 10–22 years;Early–intermediate stage of disease (1–2 progression scale) [32,33];Patient able to understand and complete the protocol (even with the help of a caregiver over 18 years of age) and perform neuropsychological tests.

Exclusion Criteria:
Undocumented genetic diagnosis of LD;Advanced stage of disease (3–4 progression scale) [32];Participation in other ongoing therapeutic treatments for LD;Pregnancy;Allergy or known hypersensitivity to empagliflozin;Other conditions, at the discretion of the investigator, that could interfere with participation or completion of the study.

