### 3.4. Outcomes

The measurement, at 3 and 6 months, of safety and clinical outcomes will be compared qualitatively with prognosis data available in the literature.

The following parameters will be determined: vital signs; weight and height; general and neurological examination; seizure diary; adverse event assessment; ECG; urine and serum pregnancy tests; laboratory tests (hematology, chemistry, and urinalysis); video-EEG/polygraphy; and high-field brain MRI (3 Tesla) and brain PET with ^18^F-fluorodeoxyglucose (at baseline and 6 and 12 months of treatment). Neuropsychological assessments will include the Montreal Cognitive Assessment (MoCA), Leiter Performance Scale 3, Visual Motor Integration test, children’s color trail test, NEPSY-II inhibition subtest, phonemic and semantic verbal fluency test, and Weiss working memory and vocabulary subtests. Motor function assessments will include the 4-stage balance test, timed up and go, 6 min walk test, 10 m walk test, 9-hole peg test, Scale for the Assessment of Ataxia (SARA), and Scale for the Assessment of Myoclonus (UMRS). Assessments of global function and autonomy will include the Lafora Disease Performance Scale (LDS), Lafora Epilepsy Severity Scale (LESS), Activities of Daily Living (ADL) and Instrumental Activities of Daily Living (IADL) scales, Barthel Index, Vineland-II Adaptive Behavior Scales, and Clinical Global Impression scales (CGI-I and PGI-CaGI-C). All assessments will be performed by the same investigator and video-recorded (with informed consent).

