## 4. Expected Results

Many of the therapeutic strategies proposed for the treatment of LD are still under investigation or have shown partial efficacy in patients, failing to halt disease progression. The expected outcomes of this study are to assess the safety and tolerability of empagliflozin in patients with LD and to gather preliminary data on its potential efficacy in improving clinical and neurologic outcomes. We recognize that the lack of a control or comparison group in the proposed single-arm observational design is a limitation. However, to mitigate the absence of a concurrent control group, we will conduct a comparative analysis using data from natural history studies, such as those evaluating metformin or VAL-1221 [9,49]. This approach will allow us to assess potential deviations from the expected disease trajectory and provide a more nuanced interpretation of the observed outcomes. Additionally, the in silico and in vitro studies, complementary and conducted in parallel with the in vivo human study, are expected to provide insights into the mechanisms through which empagliflozin may exert its therapeutic effects in LD. These findings will be important for guiding and supporting future research and development efforts aimed at repurposing empagliflozin or similar drugs for LD. By repurposing an already-approved drug, this research may significantly shorten the time and reduce the costs associated with developing a new therapy for LD patients. This has particular importance considering the rapid progression of the disease and the urgent need for effective treatment options.

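### With stage 1–2 and ages up to 22 but no account of time since onset, the literature comparison could read pre-existing slow disease as drug benefit

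*Protocol article*

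**What the plan says.** **Eligibility.** Section 2.2 of the protocol article lists "Age: 10–22 years;Early–intermediate stage of disease (1–2 progression scale") among the inclusion criteria and excludes "Advanced stage of disease (3–4 progression scale"). Neither list limits time since onset, age at onset or earlier rate of decline. In the same section, stage 2 means moderate cognitive deterioration with limits on motor and social activity. Stage 3 means severe deterioration with need for assistance, and stage 4 means wheelchair-bound or bedridden.

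**Natural course.** Section 1 states that "LD typically appears in individuals between the ages of ten and fifteen", and describes the usual end of the disease "with death occurring within eleven years of symptom onset".

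**Comparator.** Section 3.4 says: "The measurement, at 3 and 6 months, of safety and clinical outcomes will be compared qualitatively with prognosis data available in the literature". Section 4 acknowledges that there is no concurrent control and offers natural history data in mitigation: "This approach will allow us to assess potential deviations from the expected disease trajectory".

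**Favourable result.** In section 3.4, absence of worsening stands beside improvement for cognition, motor function and global function. It is also the result named for FDG-PET hypometabolism and MRI atrophy.

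**Own-patient comparison.** Tonic–clonic seizure frequency is compared with the six months before the study (section 3.4). Section 2.5 collects a full neurological history at baseline.

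**The concern.** A patient who is still at stage 1–2 many years after first symptoms has, by that fact, declined slowly. The age ceiling allows long disease durations, and the stage criterion keeps only those long-duration patients who have not declined far. If such a patient is then set against the general published prognosis, slower decline is the likely finding whether or not the drug works, because slowness formed part of how the patient came to be eligible.

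The error would favour the drug, since holding steady over six months counts as a good outcome and a slow progressor holds steady more easily. Section 2.4 plans two patients, so there is no averaging. Section 4 says that data supportive of safety and potential efficacy will lay the groundwork for larger controlled trials, so a misreading here would carry forward.

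**Working it through.** The sample size of two rests on feasibility and the analysis is descriptive (sections 2.4 and 2.6), so the plan has no calculation to reproduce. The check uses the article's own figures on age, onset and survival.

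**Step 1. Time since onset at enrolment.** Years since onset = age at enrolment − age at onset, set against the bound of 11 years.

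| Age at enrolment | Age at onset | Years since onset | Share of 11 years |
|---|---|---|---|
| 15 | 12 | 3 | 27% |
| 18 | 12 | 6 | 55% |
| 18 | 10 | 8 | 73% |
| 22 | 15 | 7 | 64% |
| 22 | 12 | 10 | 91% |

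Onset at 10 with enrolment at 22 would give 12 years, beyond the article's own bound, so that corner is not used. The table shows that the criteria admit both early patients and patients well into the usual course.

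**Step 2. Where stage 2 would usually end.** The article gives no stage durations. *Assumption for scale:* four stages spread evenly over 11 years. Stage 2 then ends at 2 × 11/4 = 5.5 years after onset, at age 15.5 (onset at 10) to 20.5 (onset at 15). A typical-onset patient aged 22 and still at stage 1–2 is past that point by at least 7 − 5.5 = 1.5 years. Because eleven years is an upper bound on survival, even spacing over 11 years probably overstates the usual time in stages 1–2.

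**Step 3. How far the stage filter enriches for slow disease (illustration only).** *Assumptions:* exponential time in each stage; mean d = 2.75 years for usual disease and 5.5 or 8.25 years for slow disease; 10% to 30% of all patients slow.

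P(still at stage 1–2 at t years) = exp(−t/d) × (1 + t/d).

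- At 2 years: 0.84 for usual disease, 0.95 to 0.98 for slow disease.
- At 7 years: 0.28 for usual disease, 0.64 to 0.79 for slow disease.

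Share slow among those still at stage 1–2 = p × P(slow) / [p × P(slow) + (1 − p) × P(usual)], with p the share slow among all patients.

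- At 2 years: about 11% to 33%, almost the starting share.
- At 7 years: from 0.1 × 0.637 / (0.1 × 0.637 + 0.9 × 0.278) = 20% to 0.3 × 0.791 / (0.3 × 0.791 + 0.7 × 0.278) = 55%.

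Under these assumptions the stage filter is nearly neutral early and roughly doubles the share of slow progressors by 7 years.

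**Step 4. What six months of stability shows.** With the same model and no drug effect, one patient keeps the same stage for six months with probability exp(−0.5/d), and both do with its square. For usual disease (d = 2.75) this is 0.83² = 0.70; for slow disease (d = 5.5 to 8.25) it is 0.83 to 0.89. With faster usual disease (d = 1.5) it is 0.51.

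**The case against.** The strongest case against the point has five parts.

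- *The criteria only permit such a patient.* They equally admit a 13-year-old one year from onset. Onset at 10 to 15 is described as typical, so a 22-year-old at stage 1–2 may have had late onset and not slow disease. This stands. A reader might infer that the study selects slow progressors or that a false benefit will appear; the text supports only that this could happen, depending on who is enrolled.
- *The literature is not the only reference.* A reader might take the external comparison as the sole substitute for a control. It is not: tonic–clonic seizure frequency is compared with the patient's own previous six months, and that endpoint is less affected.
- *Lack of alignment is inferred from silence.* A fuller document may say how published cases are chosen, and the expected course could be read as conditional on stage and duration. The stage and duration mix of the cited sources cannot be seen, so bias against those particular sources is unverified. This limits the claim. But the article does state the eligibility, the comparator and its purpose, and as stated nothing keeps selection and drug effect apart.
- *The age range is reasonable.* Section 1 counts 25 to 30 patients in Italy, so narrowing eligibility would be costly. Agreed; the remedy lies in the comparison.
- *The impact is small in a descriptive pilot.* Step 4 supports this in part: with two patients and six months, stage stability is weak evidence even in usual disease. That is a reason for caution in interpretation, and does not remove the separate problem of an unaligned reference.

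**Conclusion.** The point holds as a risk to interpretation. On the article's own figures, eligibility admits typical-onset patients 7 or more years into a course bounded at eleven, provided they are still at stage 1–2. The stated comparison with published prognosis does not take time since onset into account. Slow disease present before treatment could then be read as drug benefit in the cognitive, motor, global-function and imaging outcomes.

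This conclusion needs only the onset, survival, age and stage statements and the stated comparator. The size does rest on assumptions: the 5.5-year mark depends on even spacing of stages, and the rise to 20–55% slow progressors at 7 years depends on assumed stage durations and an assumed starting share of 10–30%. Neither is an estimate for this trial. If both enrolled patients are within two or three years of onset, the problem is slight.

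**What to change.** Leave eligibility unchanged and tighten the comparison.

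1. Take the date of first symptom from the neurological history already collected under section 2.5. Report stage and time since onset at baseline for each patient.
2. In sections 3.4 and 4, restrict the external comparison to published patients who were at the same stage at a similar time since onset, and define similar before outcomes are seen. If no published patient qualifies, say so and report that participant's course without an external comparison.
3. State in advance that a patient whose course before dosing was already slower than the usual course of the published cases cannot be read as a favourable deviation.

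Do not replace the alignment with a single pace figure such as stage divided by years since onset. With evenly spaced stages, a perfectly average patient at 3 years is in stage 2 and scores 2/3 = 0.67 stages per year, against 4/11 = 0.36 over the whole course. Average early patients would look fast.

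The cost is protocol wording and some work selecting published cases, with no new visits or tests. The downside is that fewer published cases will be usable.
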